# The effect of a telerehabilitation virtual reality intervention on functional upper limb activities in people with multiple sclerosis: a study protocol for the TEAMS pilot randomized controlled trial

**DOI:** 10.1186/s13063-020-04650-2

**Published:** 2020-08-12

**Keywords:** Multiple sclerosis, Telerehabilitation, Upper limb, Virtual reality, Pilot randomized controlled trial

## Abstract

**Background:**

Approximately 60% of people with multiple sclerosis (PwMS) suffer from upper limb dysfunction. Our primary goal is to implement a single-blind, randomized control trial (RCT) designed to compare the effectiveness of an 8-week home-based telerehab virtual reality (VR) program with conventional therapy in PwMS with manual dexterity difficulties. Secondary aims include (a) evaluating the impact of the programs on quality of life after the intervention and a follow-up 1 month later and (b) evaluating the impact of the programs on adherence and satisfaction.

**Methods:**

Twenty-four PwMS will be recruited to the study which will be conducted at two established MS centers: (1) The Regional Center for Diagnosis and Treatment of Multiple Sclerosis, Binaghi Hospital, Cagliari, Italy, and (2) The Multiple Sclerosis Center, Sheba Medical Center, Tel-Hashomer, Israel. Participants will complete a total of three assessments focusing on upper limb functions. Both groups will receive 16 training sessions focusing on functional upper limb activities. The home-based telerehab VR intervention will comprise a custom-made software program running on a private computer or laptop. PwMS will perform several activities of daily living (ADL) functions associated with self-care, dressing, and meal preparation. Conventional therapy will focus on task-related upper-limb treatments while in a sitting position, indicative of the standard care in MS. Following 8 weeks of training, participants will complete a further outcome assessment. The same tests will be conducted 1 month (as a follow-up) after completion of the intervention.

**Discussion:**

The outcomes of this study have tremendous potential to improve the quality of evidence and informed decisions of functional upper limb activities in PwMS. If comparable results are found between the treatments in improving upper limb outcomes, this would suggest that PwMS can choose the program that best meets their personal needs, e.g., financial concerns, transportation, or accessibility issues. Secondly, this information can be used by healthcare providers and medical professionals in developing upper limb exercise programs that will most likely succeed in PwMS.

**Trial registration:**

ClinicalTrials.gov NCT04032431. Registered on 19 July 2019.

## Background

Multiple sclerosis (MS) is a chronic, progressive disease of the central nervous system afflicting over 2.5 million people worldwide [1]. One of the most common reported complications is upper limb dysfunction. Several studies have described a high percentage of upper limb dysfunction in people with MS (PwMS), ranging from 50 to 76% [2, 3], which can start very early after disease onset. Upper limb dysfunction in PwMS reduces the ability to perform activities of daily living (ADLs) [4], resulting in decreased independence [5].

At some crucial point, upper limb dysfunction leads to irreversible disability resulting in secondary health conditions that are difficult, if not impossible, to treat [6]. This progression can result in decreased social, recreational, and vocational participation and ultimately to a poorer quality of life [7, 8]. The decrease in participation and work productivity combined with an increase in secondary health conditions has significantly impacted global costs [9, 10]. In Italy, at present, the rehabilitation expenditures of the MS population are approximately 27% of the direct healthcare costs of their National Health System [11].

Exercise training can improve functional activities of the upper limb and perhaps decrease the rate and extent of disability in PwMS [12–18]. Facility-based upper limb training programs, whether in a healthcare setting or laboratory, have yielded beneficial outcomes for PwMS [13–16]. However, lack of access to these programs, especially if one lives in a remote area where there are fewer options or where there are healthcare/medical facilities but no MS experts, may render it difficult to engage in traditional healthcare facility upper limb exercise training programs.

Therefore, the primary goal of the TEAMS (TElerehabilitation And Multiple Sclerosis) is to implement a single-blind, RCT designed to compare the effectiveness of an 8-week home-based telerehab VR program with conventional therapy in PwMS with manual dexterity difficulties. Secondary aims include (a) evaluating the impact of the programs on quality of life after the intervention and follow-up 1 month later and (b) evaluating the impact of the programs on adherence and satisfaction. A tertiary aim will be to generate effect sizes which can be used to power a larger clinical trial aimed at improving upper limb functional activities via telerehab in PwMS in Italy and Israel. We hypothesize that there will be no difference in outcomes between a home-based telerehab VR training program aimed at improving functional activities of the upper limbs compared with a conventional clinic-based program after the intervention and follow-up 1 month later. We also intend to corroborate a secondary hypothesis that performing the telerehab VR training will lead to better outcomes in quality of life and adherence to upper limb exercise.

## Methods/design

### Study design and settings

The study is a prospective, assessor blinded, parallel group pilot RCT. Figure 1 illustrates the study schedule. The implemented study design will adhere to the CONSORT guidelines [27] and will be conducted at two established MS centers:
The Regional Center for Diagnosis and Treatment of Multiple Sclerosis, Binaghi Hospital, Cagliari, ItalyThe Multiple Sclerosis Center, Sheba Medical Center, Tel-Hashomer, Israel

**Fig. 1 Fig1:**
[figure not shown]
Study schedule

### Methodology and work plan

Approval will be obtained from each Institutional Review Board Committee (IRB) prior to commencement. All participants will sign an informed consent form and will be randomly assigned to one of the two intervention groups:
Telerehab VR trainingConventional therapy

A block randomization procedure will be performed by the study coordinator who will place numbered tickets in sealed opaque envelopes. The sealed envelopes will be opened sequentially by the investigator only after the participant’s name and other details will be written on the appropriate envelope. The participants will be informed as to the resulting group allocation before the pre-intervention tests. The assessor will then assign the participants to an intervention program. The two interventions will be comparable in length (8 weeks), frequency (twice weekly), and session duration (50–60 min). The 8-week intervention period is in accordance with other studies investigating upper limb physical rehabilitation in PwMS [2].

Pre-intervention tests (T0) characterizing groups and obtaining baseline values of primary and secondary outcome measures will be performed 1 week ± 3 days prior to the intervention program. Within 1 week ± 3 days after completion of the intervention, post-intervention tests will be performed (T1). The same tests will be conducted at a 1 month±3 days follow-up, (T2) after completion of the intervention. During the follow-up period (T1-T2), patients will be instructed to continue their regular activities. All assessments and interventions will be performed at the two MS centers. Due to the nature of the intervention, therapists and participants will not be blinded to the group allocation; however, the assessor will be blinded. Figure 2 illustrates the procedures that participants will undergo at T0, T1, and T2.

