### Statistical analysis

Data analysis will be performed by the SPSS 25.0 program. The data will be initially examined for normality violations, outliers, errors, and patterns of missing values; missing data will be replaced by multiple imputation techniques found in the SPSS. In the event of exacerbations, the analysis will be conducted with and without the individuals who had relapsed in order to identify any untoward effects on the outcomes. The data analysis itself will follow intent-to-treat principles. The effect of the intervention on the NHPT (aim 1), ARAT (aim 1), MAM-36 (aim 1), SF-36 (aim 2), and adherence and user satisfaction (aim 3) will be examined using the Condition × Time mixed model multivariate analysis of variance (MANOVA) followed by an inspection of the univariate F-ratios. Conditions will be a between-subjects factor and time and a within-subjects factor. Interactions and main effects will be further calculated using post hoc analyses with a correction of alpha. Effect sizes associated with univariate *F*-statistics will be expressed as eta-squared (*η*^2^), and effect sizes based on a difference in mean scores will be expressed as Cohen’s *d*. We will include cognitive scores (BRB-N) as covariates in all final statistical analyses.

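### Participants learn their allocation before the T0 tests, so baseline is measured after randomisation in people who know their group and can bias the Condition × Time contrast

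*Protocol article*

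**What the plan says.** Methodology and work plan sets out the order of events. Participants consent and are randomised by sealed envelope: "The sealed envelopes will be opened sequentially by the investigator only after the participant’s name and other details will be written on the appropriate envelope". Completing the baseline tests is not a condition for opening an envelope. The text continues: "The participants will be informed as to the resulting group allocation before the pre-intervention tests".

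The next paragraph gives those tests their role and their timing relative to training: "Pre-intervention tests (T0) characterizing groups and obtaining baseline values of primary and secondary outcome measures will be performed 1 week ± 3 days prior". On blinding it says "therapists and participants will not be blinded to the group allocation; however, the assessor will be blinded".

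Under Outcomes, NHPT, ARAT, MAM-36 and SF-36 are collected at T0, T1 and T2, and BRB-N at T0 only. Statistical analysis examines the effects by a "Condition × Time mixed model multivariate analysis of variance (MANOVA) followed by an inspection of the univariate F-ratios", with BRB-N scores as covariates in all final analyses. None of the text available places T0 before disclosure. Figures 1 and 2, on the schedule and procedures, are not reproduced in the copy reviewed.

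**The concern.** A baseline is useful because allocation cannot have influenced it. Here it can. A participant who hoped for home VR and drew clinic therapy, or the reverse, may rate ability and health differently or try more or less hard on a timed task. If that reaction differs by arm, T0 differs by arm for a reason other than chance.

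T0 is one of the three occasions in the Time factor, so an arm difference at T0 feeds into the treatment-by-time contrast. The BRB-N covariates are exposed in the same way.

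The consequence can go either way. For upper limb function the article expects the two programmes to perform alike, and its sample size reasoning assumes non-inferiority, so a shifted baseline could create or hide apparent comparability. For quality of life it expects VR to do better, and SF-36 is one of the self-report scales. The tertiary aim is to produce effect sizes for powering a larger trial, so a distortion would carry forward.

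The order also opens a gap in which someone can be randomised, learn the result and leave before any T0 value exists. The intention-to-treat analysis would then rely on imputing that person's baseline.

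**Working it through.** The article states no figure for this effect, so there is none to reproduce. The first step is the order of events; the rest is illustration under stated assumptions.

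**1. Order as written.** Consent → envelope opened → participant told → T0 (NHPT, ARAT, MAM-36, SF-36, BRB-N) → training → T1 → T2. T0 is after randomisation and participants are aware of their group.

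**2. Bias in the change contrast.** Let b0 be the between-arm shift caused by knowing the allocation at T0, and b1 the shift at T1 (or T2). With no true effect, the arm difference in change from T0 has expectation b1 − b0, so the bias has size |b0 − b1|. If T0 preceded disclosure, b0 would be 0 and the bias would be b1.

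Assumed b0 = 0.2 SD (the documents give no value):

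| Persistence to T1/T2 | b1 | Bias, order as written | Bias, T0 before disclosure |
|---|---|---|---|
| None (T0 only) | 0 | 0.2 − 0 = 0.2 SD | 0 |
| Half | 0.1 | 0.2 − 0.1 = 0.1 SD | 0.1 SD |
| Full | 0.2 | 0.2 − 0.2 = 0 | 0.2 SD |

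The last column shows what reordering cannot do: it leaves any reaction still present at T1 or T2.

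**3. Effect on false-positive rate.** Simulation with 12 per arm (Sample size section), 20,000 replicates, no true effect, and change from T0 to one later occasion compared between arms at a nominal 5%. This simplifies the three-occasion MANOVA. The T0–T1 correlation is assumed. The Sample size section gives r-squared = 0.50, whose square root is 0.71, but describes it as a correlation among covariates, so a range is shown. Columns are the net shift b0 − b1.

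| Correlation | 0 | 0.2 SD | 0.3 SD | 0.5 SD |
|---|---|---|---|---|
| 0.50 | 5.2% | 7.7% | 11.0% | 21.7% |
| 0.71 | 5.0% | 9.4% | 15.3% | 33.1% |
| 0.90 | 5.0% | 18.8% | 35.2% | 74.7% |

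A shift that persists fully belongs in the zero column.

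**4. Loss before baseline.** Each participant who leaves between disclosure and T0 is 1/12 = 8.3% of an arm. The documents give no rate.

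**5. Time available for a different order.** T0 is 1 week ± 3 days before training: 7 − 3 = 4 to 7 + 3 = 10 days.

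**The case against.** The strongest reply is that participants stay unblinded throughout, so a reaction to allocation need not fade. If it persists, it cancels from the change contrast under the written order and would enter in full under the reverse order. This stands. A reader might infer that an assumed 0.2 SD shift always becomes a 0.2 SD spurious effect; that holds only for a shift confined to T0.

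Other tempting readings also go too far:

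- **That every comparison is contaminated.** The documents show that T0 can be biased, not that it is. Adherence is assessed at the end of the intervention and impression of change at T1 only, so neither is affected through T0. Direct comparisons of the arms at T1 or T2 do not use it.
- **That T0 is open-label throughout.** This is certain for participants only. The article states that the assessor is blinded, and NHPT and ARAT are performance tests given by an assessor, so exposure is clearer for MAM-36 and SF-36. The sentence "The assessor will then assign the participants to an intervention program" sits badly with that blinding, but this is a separate inconsistency. A blinded assessor cannot in any case remove a participant's own reaction.
- **That someone lost before T0 has no data.** NHPT and EDSS are inclusion criteria and the Mini-Mental State Examination an exclusion criterion, so screening values would ordinarily exist. They are not the planned baseline.
- **That baseline-adjusted ANCOVA would carry 0.14 SD (0.71 × 0.2).** The arithmetic holds for a T0-only shift, but the plan adjusts for BRB-N and specifies no ANCOVA on the baseline outcome.

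None of this supplies a reason for disclosing allocation before T0.

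**Conclusion.** The point holds as a stated, avoidable weakness in the order of procedures. It is not a detail left to a fuller document: the article says affirmatively that disclosure comes first. NHPT, ARAT, MAM-36, SF-36 and BRB-N at T0 are all measured after participants know their group, and the Condition × Time contrast uses the four outcomes' T0 values directly.

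Neither the size nor the direction of any bias can be derived from the documents. Under the assumed 0.2 SD shift it ranges from 0 to 0.2 SD according to persistence. The inflated error rates apply only to the part of the shift that is gone by T1 or T2. The loss before baseline is a possibility, not a forecast.

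The case for change does not rest on a proven bias. Testing first makes baseline a true pre-allocation measure and closes the gap between disclosure and T0, at little cost. It does not cure the expectancy effects of an unblinded comparison at T1 and T2.

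**What to change.** Reword Methodology and work plan so that the sequence is: consent; eligibility confirmed; all T0 tests, including BRB-N, completed and locked; only then the next envelope opened and the participant told. Make a completed T0 record a condition for opening the envelope.

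The cost is small but not nil. With allocation known only after T0, home installation of the VR system (Roles and mode of integration between the teams) and, unless it is run within the training period, the supervised familiarisation (Telerehab VR intervention) must fit in the 4–10 days before training. Sites should confirm that this is workable. Trial status says the trial had not begun, so the change was still open at that point.

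If the order cannot be changed, state the limitation, report by arm how many leave between disclosure and T0, and add a sensitivity comparison of the arms at T1 and T2 that does not use T0. That is a weaker fallback: with 24 participants it gives up the baseline, and it still carries any reaction present at T1 or T2. With either order, the report should acknowledge expectancy effects at T1 and T2.

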### Roles and mode of integration between the teams

Data will be shared throughout the project by personal meetings, Skype™ video calls, conference calls, and e-mail correspondence. Specifically, the Italian group will be responsible for designing and implementing three new VR scenarios relating to functional activities of the upper limb. The new VR scenarios will be planned in conjunction with the Israel group who will also play an active role in the quality assessment procedures of the developed elements. Both groups will participate equally in the pilot RCT. Roles include recruitment and guidance of patients and therapists, implementing the telerehab VR system in the patient’s home with multi-layer security, end-to-end encryption, assessment of outcome measures, and data collection. Both sites will contribute to the analysis and interpretation of data and dissemination of the findings. An additional role of the Israel team will be to prepare a user manual detailing how to use the system and providing clinical guidelines/recommendations for both the therapist and patient. Both groups will be responsible for data entry, coding, security and storage. No anticipated harm is expected; therefore, a data monitoring committee is not required. However, an independent biostatistician will be involved in the data analysis. Periodic reports on progress of the trial will be provided to the funding bodies. There is no intended use of professional writers.

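### The assessor is declared blinded, yet the same section has the assessor assign participants to their programme after allocation is revealed, so the trial's only declared blinding is contradicted by its own procedure

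*Protocol article*

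**What the plan says.** Blinding is stated in three places in the protocol article. The Background gives the aim as to "implement a single-blind, RCT designed to compare the effectiveness of an 8-week home-based telerehab VR program". Study design and settings says: "The study is a prospective, assessor blinded, parallel group pilot RCT". Methodology and work plan specifies who is covered: "therapists and participants will not be blinded to the group allocation; however, the assessor will be blinded".

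The same section, one paragraph earlier, sets out the allocation procedure by role:

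1. Preparation: "A block randomization procedure will be performed by the study coordinator who will place numbered tickets in sealed opaque envelopes".
2. Opening: "The sealed envelopes will be opened sequentially by the investigator only after the participant’s name and other details will be written" on the envelope.
3. Disclosure: "The participants will be informed as to the resulting group allocation before the pre-intervention tests".
4. Assignment: "The assessor will then assign the participants to an intervention program".

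The only other safeguard mentioned is in Roles and mode of integration between the teams: "However, an independent biostatistician will be involved in the data analysis". That person is described as independent, not as blinded.

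**The concern.** Assigning a participant to VR or to conventional therapy requires knowing which of the two was drawn. The person who does this in step 4 is called the assessor, the same term used for the one party declared blinded. The two statements cannot both be true of the same person.

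Participants and therapists are open by design, so assessor blinding is the only stated protection against detection bias. Exposure differs by outcome:

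- **ARAT:** tasks are observed and rated 0 to 3, so it is the most exposed.
- **NHPT (primary):** this is a recorded completion time. Instruction, encouragement and the start and stop of timing pass through the tester. That is an inference about how such a test is run; the article does not say it.
- **MAM-36:** the participant gives the ratings, but in a semi-structured interview.
- **SF-36, diaries and USEQ:** these come from participants who know their arm, so assessor blinding protects them little.

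The direction of a lean matters because the main hypothesis is no difference between arms. The Discussion would read comparable results as grounds for patients to choose either programme. A lean towards VR could produce or hide such a result, and it would carry into the effect sizes meant to power a larger trial.

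**Working it through.** **Text check.** The question is whether the passages can be reconciled.

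- *Could the assessor in step 4 be another named role?* The coordinator, the investigator and the therapists are each named separately in the article. Nothing equates the assessor with any of them.
- *Could there be two assessors?* No section names a second one, or says that T0, T1 and T2 are measured by someone other than the person who assigns.
- *Could the order of events preserve blinding?* The word *then* can mean after the participant is told the group (before T0) or after the T0 tests. On the first reading, which is the natural one, the assessor knows the arm at T0, T1 and T2. On the second, T0 is protected but T1 and T2 are not, and those visits carry the treatment comparison.
- *Is any other party blinded?* None is stated.

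The contradiction therefore stands on every reading the article allows.

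**Illustration of size.** The plan gives no figure for this, so there is none to reproduce. From Sample size come n = 12 per group, alpha 5% (sidedness not given) and R-squared 0.50. The lean *b* (0.1 or 0.2 SD towards VR) and the one-sided test are assumptions.

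Standard error of the difference, in SD units:

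- with covariates: sqrt(1 − 0.50) × sqrt(2/12) = 0.289
- without the R-squared reduction: sqrt(2/12) = 0.408

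The error rate under a lean *b* is 1 − Φ(z − b/SE), with z = 1.645 for one-sided 5% and 1.960 for one-sided 2.5%. In the leading case:

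- b = 0.1: 1 − Φ(1.645 − 0.346) = 1 − Φ(1.298) = 9.7%
- b = 0.2: 1 − Φ(1.645 − 0.693) = 1 − Φ(0.952) = 17.1%

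The range over the assumptions:

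| SE (SD) | Nominal one-sided level | Lean 0.1 SD | Lean 0.2 SD |
|---|---|---|---|
| 0.289 | 5% | 9.7% | 17.1% |
| 0.289 | 2.5% | 5.3% | 10.3% |
| 0.408 | 5% | 8.1% | 12.4% |
| 0.408 | 2.5% | 4.3% | 7.1% |

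Across these cases the nominal rate is multiplied by between about 1.6 (8.1/5) and 4.1 (10.3/2.5).

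**The case against.** The strongest reply is that this is a slip of the pen. Blinding intent is stated three times, the roles are otherwise kept apart, and the article condenses a full protocol (version 2.0) that is not shown. One odd sentence may simply name the wrong role. That is a fair point about what may happen in practice, and the article does not prove that the assessor will be unblinded. It does not remove the fault: the article gives two explicit instructions that conflict, and a misnamed role needs correcting too.

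Several narrower objections have force:

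- Unblinding at T0 depends on how *then* is read; unblinding at T1 and T2 does not.
- Outcomes are not equally exposed, and assessor blinding gives patient-reported measures little protection.
- Non-inferiority appears only in a parenthesis in Sample size, without a margin, and the planned analysis is a Condition × Time MANOVA. No non-inferiority decision rule is stated for a lean to tip. The argument about direction rests instead on the hypothesis of no difference and on the use the Discussion makes of comparable results.
- The numerical illustration uses leans with no source and a choice of sidedness the article does not make. It is therefore shown as a range, and the conclusion does not rest on it.
- Recording assessor guesses and similar measures go beyond what the contradiction requires.

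**Conclusion.** The concern holds and should be fixed before enrolment. As written, the procedure gives the assessor knowledge of the arm before T1 and T2 on any reading, and before T0 on the natural one. Since no other party is declared blinded, following the procedure leaves the trial without effective blinding. The observer-rated ARAT is the most exposed outcome; the primary NHPT is exposed through the conduct and timing of the test.

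The size of any bias is unknown. If the lean were 0.1 to 0.2 SD, the nominal error rate would be inflated roughly 1.6 to 4 times, depending on sidedness and covariate adjustment. The conclusion assumes only that *the assessor* means the same role in both sentences, as the article's wording implies. It is a finding about the stated procedure, not about what any site has done.

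**What to change.** **Required.** Reword the assignment sentence so that the study coordinator or the treating therapist, not the assessor, communicates the allocation and assigns the programme. Add that the person who measures T0, T1 and T2 has no access to the envelopes, the allocation list, the VR set-up or the therapy bookings. If the full protocol already provides for a separate outcome assessor, say so here.

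**Advisable, but not needed to resolve the contradiction.** Ask participants not to disclose their arm to the assessor. Record the assessor's guess of the arm at T1 and T2, so that the success of blinding can be reported.

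**Cost.** The required change moves one task between existing staff and amends a sentence, with a short statement on access. The optional items add an instruction and one recorded question per visit. Trial status says the trial has not begun, so no data are affected.
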